#### Statistical methods for secondary outcomes

Secondary analyses based on *p* values adjusted for multiple comparisons included fitting regression models to determine the impact of the intervention on linkage to care within 7 days, ART initiation, ART adherence, and retention in care at 12 months. To evaluate ART adherence, we will compare the binary outcomes and continuous values for hair tenofovir concentration between study arms. The effect of the intervention on quality of life will be assessed using mixed effects linear regression by comparing the intervention and control groups. We will also evaluate changes in quality of life measured over 12 months by paired *t*-test. Finally, we will evaluate sex as a biological variable to assess whether the intervention’s effect differs between men and women.

For the implementation evaluation, quantitative analysis will proceed with a descriptive statistical analysis for continuous variables such as the TFA and fidelity scores. Outcomes will be compared across TH and HIV clinician sociodemographic characteristics using logistic regression and mixed linear models. Mixed effects logistic regression models will be used to assess intervention maintenance using HIV viral load in blood plasma samples.

#### Qualitative and mixed methods analysis

Qualitative data analysis will incorporate a priori codes from CFIR domains to generate initial codes. The iterative nature of data collection will also allow for the inclusion of emerging codes in the codebook. English transcripts will be read and coded by the Qualitative Data Coordinator and US principal investigator. Codes will be harmonized, reviewed, organized into themes, and examined to identify patterns pertinent to implementation constructs. Collaborators will review the data twice per month to determine, through consensus, when theoretical saturation has been reached. NViVo 11 (QSR International Pty Ltd.) will be used for data organization.

A convergent mixed methods approach will assign equal weight to qualitative and quantitative data to evaluate aspects of intervention implementation according to the domains in Table 2. We will evaluate qualitative and quantitative datasets to identify areas of convergence and discordance [71]. Trends in the survey data regarding implementation context and outcomes will be examined and merged with pertinent qualitative findings using a joint display approach [72]. The data will be triangulated to investigate various variable relationships, for example, correlations between PLWH, TH, and HIV clinicians’ attitudes toward viral load suppression or how qualities of internal settings align with successful collaborations between TH and HIV clinicians.

### Oversight and monitoring

The study has an Administrative Core, Steering Committee, and Data Safety and Monitoring Board (DSMB). The Administrative Core comprises the study principal investigators, a full-time Ugandan project manager, and a full-time US research coordinator. Together, they oversee trial activities and regulatory requirements and coordinate team meetings. The Steering Committee comprises principal investigators, coinvestigators, a project manager, quantitative and qualitative data managers, and two Ugandan research assistants. This committee ensures adherence to the study protocol and standard operating procedures to achieve the stated research goals.

The three-person DSMB is an independent external monitoring committee that includes a biostatistician, clinical trialist, and HIV clinician. The DSMB met prior to study initiation to review the consent forms and protocol and will meet every 6 months throughout the study period or more frequently as needed. Prior to their meeting, the DSMB will receive open reports of study progress and all adverse events (please see below), including breaches of confidentiality, stigma, and social harm. After the 325th participant has been enrolled, the DSMB will be presented with interim analysis results and decide whether to terminate, modify, or continue the trial.

### Adverse event reporting and harms

An adverse event (AE) is defined as any untoward medical occurrence in a participant regardless of the possibility of a causal relationship to trial participation [73]. All adverse events occurring after the point of enrollment will be collected systematically from each participant. At each study visit, participants will be asked whether they “have experienced any problems as a result of being in this study.” All AEs reported after enrollment and through the end of the study period will be defined and graded for severity based on guidance from the Health and Human Services Office of Human Research Protections [73]. The suspected relationship to trial intervention will be determined by the principal investigators and documented along with the interventions given and the outcome. This documentation will be reported to the local Institutional Review Board (IRB), the DSMB, and the trial sponsor.

A serious adverse event (SAE) is any event that is fatal or life-threatening, results in persistent or significant disability or incapacity, constitutes a congenital anomaly or disability, or requires inpatient hospitalization or prolongation of existing hospitalization [73]. An SAE may also include an event that is sufficiently significant to require medical or surgical intervention to prevent one of these serious outcomes or is a hazard determined by the DSMB. An AE that meets the criteria for an SAE between enrollment and the end of the study will be reported to the local IRB, the DSMB, and the trial sponsor.

The decision for study discontinuation of a study participant will be made by the principal investigators and/or the study participant. Study personnel will document the circumstances and data leading to discontinuation. The principal investigators will receive a weekly log of any AEs and will review this log each week with the Administrative Core.

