### Participant timeline

Please see Table 3 for the detailed schedules of activities for each participant group.

**Table 3 Tab3:** Detailed schedules of activities for each participant group

People Living with HIV (PLWH) Schedule of Activities							
**Period/Phase**	**Screening/Baseline**	**Day 15**	**Day 29**^**d**^	**Day 43**^**d**^	**Day 57**^**d**^	**12-Month F/u**	**24-Month F/u**
**Study Day**	**D1**	**D15**	**D29**	**D43**	**D57**	**D365**	**D731**
**Study Week**	**W1**	**W2**	**W4**	**W6**	**W8**	**W52**	**W104**
**Study Visit**	**1**	**2**	**3**	**4**	**5**	**6**	**7**
**Window (Days)**		** ± 7**	** ± 7**	** ± 7**	** ± 7**	** + 30**	** + 30**
Oraquick HIV Testing^a^	x						
Case Adherence Index Questionnaire^b^	x						
Informed Consent	x						
Assessment of Inclusion/Exclusion Criteria	x						
Demographic Collection^c^	x						
Medical History	x						
HIV History	x						
FSSQ [56]	x					x	x
HIV-ASES [57]	x					x	x
HIV Stigma Questionnaire [58]	x					x	x
HIV-SMS [59]	x					x	x
HIV-KQ-18 [60]	x					x	x
Quality of Life (MOS-HIV) [61]	x					x	x
TFA [62]	x					x	x
Dried Blood Sampling						x	x
Hair Sample Collection						x	
Patient Enrollment card	x					x	x
**Interviews (will be conducted for specified patients)**	x					x	x
*Perceived complexity and relative advantage of the intervention*	x					x	
*Perceived successful strategies with implementers & patients*	x					x	
*Perceived roles of intervention champions & opinion leaders*	x					x	
*Facilitators & barriers to implementation*						x	
*Sustained impact of intervention on HIV continuum of care*							x
*Integration into routine practice; reasons for maintenance/discontinuation*							x
Phone Call to Patient about Linkage to HIV Care		x	x	x	x		

^a^Oraquick HIV Testing to be administered prior to study enrollment to adults reporting no prior HIV diagnosis or HIV testing within the prior 12 months

^b^Case Adherence Index Questionnaire to be administered prior to study enrollment and to suspected defaulting participants only

^c^Demographics include includes age, sex, education, religious affiliation, household size, marital status, highest level of education

^d^Visit only occurs if PLWH has not linked to care within 7 days

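### Adverse events are defined regardless of cause, but the only elicitation question the article states asks about problems resulting from the study

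*Protocol article*

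**What the plan says.** All of the safety wording is in two sections of the protocol article.

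Under 'Adverse event reporting and harms', an adverse event is "any untoward medical occurrence in a participant regardless of the possibility of a causal relationship to trial participation". On scope, the section states: "All adverse events occurring after the point of enrollment will be collected systematically from each participant". It then gives one question, asked at each study visit: whether participants "have experienced any problems as a result of being in this study". On causality: "The suspected relationship to trial intervention will be determined by the principal investigators". The rule for serious events has no attribution condition: "An AE that meets the criteria for an SAE between enrollment and the end of the study will be reported". The recipients named are the sponsor, the DSMB and the local review board. The principal investigators also receive a weekly log of adverse events.

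Under 'Oversight and monitoring', before its meetings "the DSMB will receive open reports of study progress and all adverse events (please see below), including breaches of confidentiality, stigma, and social harm". The board "will meet every 6 months throughout the study period", or more often if needed.

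The occasions for asking are set by 'Participant timeline'. In-person study visits are at baseline, 12 months and 24 months. Table 3 adds phone calls about linkage to care on days 15, 29, 43 and 57. A footnote attached to the last three reads: "Visit only occurs if PLWH has not linked to care within 7 days".

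**The concern.** The definition and the stated tool do not match. Under the definition, the event is recorded first and its cause is judged afterwards by the investigators. Under the question, the participant judges the cause first, and only events that pass that judgement are mentioned. A participant admitted to hospital with an illness they see as nothing to do with the trial can truthfully answer no, and the investigators then have nothing to grade.

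What is at stake is safety ascertainment. Everyone enrolled has an unsuppressed viral load, so illness and hospital admission during two years of follow-up are plausible in both arms. If they are not asked about, the DSMB may read a short list of events as reassurance when it partly reflects how the question was put.

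**Working it through.** No formula or planned figure applies to the main point. It rests on setting the stated rules side by side and asking what each does with the same event.

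1. *An illness or hospital stay that the participant does not attribute to the study.* By the definition it is an adverse event. By the collection statement it is to be collected. If it involves inpatient admission, it meets the serious-event criteria and is reportable. By the stated question it is not asked for. The rules disagree.
2. *A breach of confidentiality, stigma or social harm arising from taking part.* The DSMB is to see it, and the question asks for it. Here the rules agree.
3. *Relatedness.* The section assigns it to the principal investigators. The question has the participant apply it beforehand. The investigators can grade only what is reported, so an event filtered out at this step is never graded.
4. *Other routes.* The serious-event rule and the weekly log say where events go. Neither says how an event that the participant does not attribute to the study is first found.

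The conflict is therefore confined to events of type 1.

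Next, how often the question can be asked, using the study days in Table 3:

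- Linked within 7 days: the last early contact is day 15 and the next is day 365. 365 − 15 = 350 days. With the 7-day window used in full, 365 − 22 = 343 days.
- Not linked within 7 days: the last early contact is day 57 at the latest. 365 − 57 = 308 days.
- Both groups, between the 12- and 24-month visits: 731 − 365 = 366 days.

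The first two lines are generous to the plan, because Table 3 gives the early calls no purpose other than linkage. If the question is not asked on them, the gap from baseline is 365 − 1 = 364 days. The DSMB meets about every 183 days, so each of these gaps spans at least one meeting. Such a schedule is a choice open to a low-risk behavioural trial and is not an error in itself. It does mean that the wording used at the few shared contacts carries much of the weight.

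**The case against.** The strongest reply is that this is a condensed article. Adverse event forms and serious-event procedures usually sit in the full protocol, which is not shown. The article nowhere calls the quoted question the sole route, and a weekly log suggests some intake between visits. This stands as far as it goes: a reader might infer that adverse events are elicited by this question alone, and the text does not say so. It does not remove the conflict, because the wording of the question is stated, not left out.

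A second reply is that the harms named for the DSMB are mostly study-related and the question suits them. That is also correct. A reader might infer that the events the board is there to review will be missed; the article does not support this. The events at risk are those not attributed to the study, and they may be under-ascertained, which is weaker than certainly lost.

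A third reply is that the article calls its procedures minimally invasive and low risk, so collecting only study-related harms would be defensible. It might be, but the article commits to something wider: all events, whatever their cause.

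A reader might also infer biased reporting between arms, since intervention participants see their healer weekly and then monthly. No section says that healers report adverse events, healers in both arms receive phone vouchers for contact with study staff, and no between-arm comparison of adverse events is described. That inference is speculation and forms no part of this point.

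**Conclusion.** The point holds in a limited form. The adverse event definition and the only elicitation question the article states are in conflict. Medical events that participants do not attribute to the study are likely to be under-ascertained in what reaches the DSMB. This assumes that the question is asked as worded and that no other active enquiry, described only in the full protocol, picks these events up.

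The size cannot be computed. A reader might try to put a percentage on the events missed, but the article gives no rate of illness and no rate of attribution. Any such figure would be the complement of an assumed one, with every other route set to zero.

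The primary outcome is a laboratory measurement of viral load and does not pass through this question. The primary analysis, significance level, power and sample size are untouched. The change is still worth making, because it is cheap and the present wording works against the section's own stated aim.

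**What to change.** Replace the question with a causality-neutral one, for example: *since we last spoke, have you had any health problem, hospital stay or harm of any kind?* Keep a second, separate prompt for problems linked to taking part (confidentiality, stigma, social harm), which the present wording serves well. Investigators grade relatedness afterwards, as already planned.

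Ask both items in the same words in both arms, at contacts that every participant has: the 12- and 24-month visits and, if an earlier point is wanted, the day-15 call. Do not add them to the calls on days 29 to 57. Those occur only for participants not linked within 7 days, and rapid linkage is what the intervention aims to change, so the number of times a participant is asked could then differ by arm.

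The cost is one revised form item, one additional prompt, and more unrelated events to grade. No visit is added. The change does not shorten the long interval between shared contacts, and no participant question can pick up deaths, which still depend on the serious-event reporting rule. If the sponsor in fact intends to collect only study-related harms, the definition, the statement on systematic collection and the DSMB's remit should be narrowed to say so.

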### Plans for communicating important protocol amendments to relevant parties

The Mbarara University of Science and Technology Ethics Committee and Weill Cornell Medicine IRB will be notified of all protocol amendments as per regulations provided by the respective parties. Trial participants will be notified by telephone of changes to the trial protocol and will be reconsented if necessary.

### Dissemination plans

The trial has been registered on ClinicalTrials.gov, and the record will be updated at least once per year and within 30 days of a change to applicable sections of the ClinicalTrials.gov record. Final trial results will be posted on ClinicalTrials.gov no later than 1 year after the study’s primary completion date. Preliminary results will be presented twice per year to our ten-person traditional healer Community Advisory Board and to the local academic community at the annual Mbarara University of Science and Technology Research Dissemination Conference. In addition, we will organize annual dissemination meetings with officers from the Ugandan Ministry of Health AIDS Control and Community Health Divisions, along with stakeholders from civil society organizations. Scientific abstracts will be submitted to international and domestic conferences, and trial results will be submitted for publication in peer-reviewed journals, with all publications as open access.

## Discussion

While there is observational evidence suggesting that TH can be leveraged as lay providers to improve engagement in HIV care, there is a dearth of systematic trials addressing this subject [34, 39, 74–76]. This clinical trial is essential for definitively evaluating the impact of TH-supported care on HIV suppression in rural communities and optimizing the allocation of programmatic resources to low-income contexts. The implementation science approach employed in this study can accelerate evidence into practice by collecting data pertinent to intervention effectiveness concurrently with data on the implementation context, facilitators and barriers to program success. If successful, this approach could transform HIV programming in rural regions where PLWH face numerous barriers to entering and remaining with HIV and support progress toward the UNAIDS 2030 goals to end the HIV epidemic [5].

There are some limitations to this study, which include that it is being evaluated in a geographically limited area of rural Uganda. However, we designed the implementation evaluation of this study using the CFIR to rigorously evaluate the contextual drivers affecting the delivery and effectiveness of the intervention. These types of data have been successfully applied to guide adaptations and delivery of numerous evidence-based programs, and we anticipate a similar ability to generalize findings to improve HIV outcomes across Uganda and other African countries where TH are ubiquitous members of rural communities [31, 77, 78].

### Trial status

Protocol 2.0 version date: September 29, 2023.

Date recruitment began: July 7, 2023.

Approximate date of recruitment completion: July 30, 2025.

## Data Availability

The final de-identified dataset will be available upon request made to the first author and following the completion of a data-sharing agreement.

## Abbreviations

AE: Adverse event
ART: Antiretroviral therapy
CFIR: Consolidated Framework for Implementation Research
DSMB: Data Safety and Monitoring Board
HIV: Human immunodeficiency virus
IRB: Internal Review Board
PLWH: People living with HIV
SAE: Serious adverse event
TH: Traditional healer
